## 3.2 Significance and Scientific Rationale

Malaria prevention measures for pregnant women are critical and available, but the effectiveness of IPTp with SP, a cornerstone in this prevention effort, is declining with increasing parasite resistance. New drugs for IPTp are being considered, but there are disadvantages to presumptive use of the few remaining efficacious antimalarials. An alternative approach may involve screening with diagnostic tests to better target efficacious antimalarial treatment to asymptomatic women with laboratory evidence of malaria infection. Light microscopy of peripheral maternal blood misses a large proportion of cases, and PCR is unavailable in routine health care settings. Preliminary evidence suggests that detection of parasite antigen in peripheral blood may provide an accurate indicator of clinically significant infections and predict pregnancy outcomes. Therefore, screening with RDTs may offer an accurate and practical way to identify pregnant women who will benefit from targeted therapy for placental malaria infection. Antigen detection thresholds vary widely among RDTs, and the distribution of target antigens in peripheral blood circulation is expected to differ; therefore, the potential value of RDTs in this population can best be established by evaluating the detection of placental parasitemia for highly-characterized RDTs, enabling results to be extrapolated to other products and programs. The study described below is proposed to address this question.

1. **STUDY OBJECTIVES**

## 4.1 General objective

To determine whether screening pregnant women for malaria with RDTs may detect placental infection and predict risk of poor birth outcomes due to malaria in areas of varied malaria transmission in Africa.

Specific primary objectives:

1. To compare the results of RDTs, microscopy and PCR performed on peripheral blood from women in the second and third trimesters of pregnancy in malaria-endemic areas of Africa.
2. To determine the positive and negative predictive values of results of RDTs, microscopy and PCR performed on peripheral blood from women in the second and third trimesters of pregnancy, as compared with evidence of placental infection by histological examination after delivery.

Specific secondary objectives:

1. To measure and compare the frequency of pregnancy outcomes (infant birth weights, maternal hemoglobin), prevalence of placental malaria, and risk of symptomatic malaria among women in the study cohort. Participants who test positive by RDT at the time of usual IPTp administration will receive artemisinin-combination treatment (ACT) or quinine; participants who test negative by RDT will receive standard-of-care IPTp with SP.
2. To collect samples for future laboratory analyses related to malaria in pregnancy, including the measurement of the prevalence of molecular markers of antimalarial resistance in the study cohorts.
3. **STUDY DESIGN**

(See Figure 1 on next page.) Women will be enrolled at their initial presentation for antenatal care after quickening, i.e. on the first antenatal visit when they are eligible for IPTp according to WHO recommendations.2 On the usual IPTp schedule, typically once in the second and once in the third trimester, blood will be collected from all participants for RDT testing, preparation of thick and thin smears for light microscopy, and PCR. RDTs detecting histidine-rich protein 2 (HRP2) and plasmodium lactate dehydrogenase (pLDH) will be used for testing. All participants with negative RDT results will receive SP, and those with a positive RDT result will receive ACT or quinine (according to national policy for treatment of malaria in pregnancy). All participants will be followed up to delivery. At delivery maternal peripheral and placental blood samples will be collected for RDT testing, light microscopy, and PCR, and placental tissue samples will be processed for histopathological examination. Measurement of maternal hemoglobin and infant birth weight will be obtained.

**Figure 1. Patient flow diagram to evaluate association of RDT results with evidence of placental malaria infection and pregnancy outcomes**

**Pregnant woman presents for routine antenatal care “after quickening” and before onset of labor**

**Study enrollment**

- All selection criteria met
- History & clinical exam
- Venous blood for Hb, RDTs, thick/thin smear, and storage in EDTA, red cell pellet and filter paper for PCR
- Provision of other standard care (ITN, iron + folate supplementation, etc) according to national guidelines

**RDT positive**

**(either HRP2 or pLDH)**

**RDTs negative**

**(both HRP2 and pLDH)**

- **DOT IPTp with SP**
- Management of any symptoms at clinician’s discretion according to national guidelines and standard of care
- **ACT (according to nat’l policy)**
- Management of any symptoms at clinician’s discretion according to national guidelines and standard of care
- **Follow up 2 weeks later for DOT IPTp with SP**

**Subsequent routine antenatal visit/s**

(≥ 1 month after previous visit and before onset of labor)

- History & clinical exam
- Venous blood for Hb, RDTs, thick/thin smear, and storage in EDTA, red cell pellet and filter paper for PCR
- Provision of other standardized care (ITN, iron + folate supplementation, etc) according to national guidelines

**RDT positive**

**(either HRP2 or pLDH)**

**RDTs negative**

**(both HRP2 and pLDH)**

- **DOT IPTp with SP**
- Management of any symptoms at clinician’s discretion according to national guidelines and standard of care
- **ACT (according to nat’l policy)**
- Management of any symptoms at clinician’s discretion according to national guidelines and standard of care
- **Follow up 2 weeks later for DOT IPTp with SP**

**Follow up at delivery**

- Maternal peripheral blood for Hb, RDTs, smear, and PCR
- Placental blood for RDTs, smear, and PCR
- Placental tissue sample to process for histopathological examination
- Measurement of infant birth weight
- (Other data on any maternal or fetal morbidity/mortality)

1. **STUDY POPULATION**

Participants in this evaluation will include pregnant women presenting for routine antenatal services in areas of Africa where IPTp is considered standard of care according to WHO and national malaria control program guidelines. Pregnant women of any parity will be eligible for enrollment. Anticipated sites include antenatal clinics in Burkina Faso, Nigeria, and Uganda. Specific participant selection criteria will include (please see also section 7.2 on participant enrollment):

1. Presenting for care after quickening and before onset of labor (i.e. in the second or third trimester of pregnancy)
2. Age between 16 years and 44 years, inclusive
3. Willingness and ability to follow up with study visits and activities through the duration of pregnancy and at delivery
4. Absence of history of serious adverse reaction to sulfa drugs
5. Absence of history of serious adverse reaction to artemisinin-based drugs or quinine (depending on national policy on treatment of malaria in pregnancy)
6. Absence of HIV infection (both because guidelines for malaria prevention in pregnancy for HIV-infected women differ from those for HIV-negative women, and in order to avoid confounding of pregnancy outcomes by HIV-related complications or treatments in this early evaluation)
7. Absence of history of or current obstetrical complications (e.g. pre-eclampsia, eclampsia, hypertension during pregnancy, post-partum hemorrhage, evidence of multiple gestation)
8. Absence of chronic disease (e.g. diabetes mellitus, sickle cell disease)
9. Absence of evidence of severe acute disease requiring inpatient management or referral
10. Provision of written informed consent
11. Enrollment Hb ≥7 g/dL

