***(End Uganda site-specific information.)***

*7.3.5 Scheduling of subsequent visit/s*

The participant will be encouraged to return to the study site for her subsequent routine antenatal visit/s, and if feasible, for any intervening care-seeking. Subsequent antenatal visits will be scheduled according to the national standard of care, typically including at least one visit in the second trimester and one visit in the third trimester. Routine visits will be scheduled at least 4 weeks apart; participants will not receive more than one dose of SP within any 4-week period. Each participant will be given a card/booklet with dates of future study visits, and in which to record any care or treatment that is received from non-study site providers between routine visits.

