Each lot of RDTs will undergo lot testing according to WHO guidelines57 before and at the end of the study. RDT testing will take place in the laboratory of [name] at the Centers for Disease Control and Prevention (CDC), Atlanta, Georgia, USA. Prior to the start of the study activities at each site, the RDTs to be evaluated will be stored in their original packaging at room temperature in a central storage space. Stocks of RDTs, adequate to complete training and the study at each site, will be transported to each health center prior to the training and pilot period at each site. Manufacturers recommend that RDTs be stored between 4 and 40° C. Temperature and humidity of the storage areas will not be controlled, but will be monitored and recorded regularly to document storage conditions at each site.

*7.6.2.2 RDTs to be evaluated*

The following criteria will be considered in selecting the RDTs for this evaluation: high performance in WHO/FIND standardized product testing,27 ease of use, safety (minimal exposure to blood during test preparation), completeness of packaging, appropriate packaging for transport and storage in tropical environments (each test individually wrapped in foil with plastic liner), reasonable market price, and reliability of the supply of the RDTs.

*7.6.2.3 Preparation of RDTs*

RDTs will be performed on maternal blood obtained by venipuncture at the time of each routine antenatal visit, and at the time of delivery. In addition, RDTs will be performed on placental blood obtained at delivery. Individual RDTs will be labeled with the participant’s unique study number and initials. A member of the study staff will prepare the RDTs according to manufacturer instructions. All personnel will use universal precautions when handling blood samples.

*7.6.2.4 Interpretation and recording of RDT results*

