Before the commencement of field work, designated microscopists at each site will be pre-qualified through blinded readings on slides prepared according to the WHO slide bank protocol, and required to reach level 1 or 2 expertise level (as described in the WHO Malaria Microscopy Quality Assurance Manual, version 1, Chapter 5).58 All slides collected during the study at each site will be read by two microscopists. Slides with discrepant results will be re-read by a third external reader (Level 1 WHO microscopist) and returned to the study site after reading. In addition, 10% of slides from each site will be sent for review at an internationally recognized center of excellence for malaria microscopy. All microscopists will be blinded to RDT results and to results of previous microscopy.

*7.6.4 PCR for detection and speciation of parasitemia*

As for RDT and blood smear preparation, at the time of each routine antenatal visit and at delivery, two drops of maternal blood will be collected onto filter paper and 250uL into a microtainer containing EDTA anticoagulant. In addition, at the time of delivery, placental blood will be collected onto filter paper and into EDTA microtainer/s. Each filter paper sample will be labeled with the participant’s study number, air-dried, and stored in a sealed plastic bag at ambient temperature. Microtainers will be labeled with the participant’s study number and stored at -20°C. Samples will be transferred to a central laboratory and analyzed by PCR to confirm presence or absence of parasitemia, and parasite species. PCR will be performed at the laboratory of [name] in Bobo-Dioulasso, Burkina Faso, and quality assurance of results will be conducted at the laboratory of [name] at the Centers for Disease Control and Prevention, Atlanta, Georgia, USA.

*7.6.5 Estimation of gestational age*

At enrollment, duration of gestation and expected delivery date will be estimated by reported last menstrual period (LMP) and by measurement of fundal height, and these data will be recorded on the participant’s case record forms. At subsequent study visits, fundal height will be measured and recorded.

*7.6.6 Measurement of infant birth weight*

Within 24 hours of delivery, study staff will weigh the infant on a calibrated scale. Birth weight will be recorded in grams; based on WHO definitions, low birth weight (LBW) will be considered < 2500 g.

*7.6.7 Placental histopathology for detection of evidence of prior or current placental malaria*

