**11.1 Study outcome measures**

Results of peripheral blood tests performed during gestation will be analyzed for associations with evidence of placental malaria and pregnancy outcomes. The statistical analysis will focus on three primary outcomes: 1) negative predictive power of malaria RDTs, peripheral blood films and PCR performed on peripheral blood to diagnose placental malaria during gestation, 2) association of placental malaria during gestation on mean infant birth weight and 3) association of placental malaria during gestation on mean maternal Hb. These outcomes will be used to assess the potential utility of RDTs as screening tests to identify clinically significant malaria infections at a time when effective preventive measures may be taken. Other factors known to influence the study outcomes, including iron and folate supplementation, bed net use and administration of antihelminthic drugs will be treated as confounders in the analysis. In addition, stratified analysis will be conducted to assess these associations within subgroups based on geographic location, estimates of malaria endemicity, participant age, and parity (gravida class).

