**11.2 Analysis plan**

The unit of analysis will be each pregnancy. For each pregnant woman a complete data set consists of the following:

| Variable | Type of data | Variable classification | | | | |
| --- | --- | --- | --- | --- | --- | --- |
| Confounder | Evidence of placental malaria | Outcome measure | | |
| Predictive value of diagnostic | Infant birth weight | Maternal Hb |
| RDT on peripheral blood taken during 2nd trimester | Binary (positive / negative) |  |  | X |  |  |
| Microscopy of peripheral blood taken during 2nd trimester | 1. Binary (positive / negative)  2. Count for positives |  |  | X |  |  |
| PCR on peripheral blood taken during 2nd trimester | Binary (positive / negative) |  | X |  |  |  |
| RDT on peripheral blood taken during 3rd trimester | Binary (positive / negative) |  |  | X |  |  |
| Microscopy of peripheral blood taken during 3rd trimester | 1. Binary (positive / negative)  2. Count for positives |  |  | X |  |  |
| PCR peripheral blood taken during 3rd trimester | Binary (positive / negative) |  | X |  |  |  |
| RDT on peripheral blood taken during or shortly after delivery | Binary (positive / negative) |  |  | X |  |  |
| Microscopy of peripheral blood taken during or shortly after delivery | 1. Binary (positive / negative)  2. Count for positives |  |  | X |  |  |
| PCR result on peripheral blood taken during or shortly after delivery | Binary (positive / negative) |  | X |  |  |  |
| Placental histology for evidence of infection | Binary (positive / negative) |  | X |  |  |  |
| Diagnostic results of any additional visits to clinic (eg symptomatic infection) | Binary (positive / negative) |  | X |  |  |  |
| Maternal Hb at delivery | Continuous |  |  |  |  | X |
| Infant birth weight at delivery | Continuous |  |  |  | X |  |
| Study site | Nominal | X |  |  |  |  |
| Age | Continuous | X |  |  |  |  |
| Gravidity | Ordinal | X |  |  |  |  |
| SP treatment | Binary (yes/no) | X |  |  |  |  |
| Iron & folate supplementation | Binary (yes/no) | X |  |  |  |  |
| Bed net use | Binary (yes/no) | X |  |  |  |  |

The following definitions will be used:

- Evidence of placental malaria: a positive PCR result is obtained for any peripheral blood sample and / or there is evidence of placental infection by histology
- RDT positive: a positive RDT result is obtained from one or more blood samples
- Microscopy positive: parasites are detected by microscopy (thick film) in one or more of the blood samples

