The accuracy of RDTs and peripheral microscopy at detecting placental malaria will be assessed by considering the sensitivity, specificity, positive predictive value and negative predictive value of each diagnostic compared to evidence of placental malaria. This analysis will be conducted for all samples combined and also separately for each study location. Marginal generalized linear models will be developed to assess the impact of confounders on predictive values.

The impact of RDT screening and treatment compared to standard IPT on infant birth weight and maternal Hb will be assessed for non-inferiority by testing the hypotheses:

1. Mean birth weight of infants whose mothers were RDT positive & treated with ACT/quinine ≥ mean birth weight of infants whose mothers were RDT negative (and received SP)
2. Mean Hb of mothers who were RDT positive & treated with ACT/quinine ≥ mean Hb of mothers who were RDT negative (and received SP)

Standard statistical techniques such as t-tests, ANOVA and regression modeling will be used to test these hypotheses and investigate the potential impact of confounders on birth weight and maternal Hb.

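### Gestational age at enrolment is recorded but missing from the section 11.2 confounders, so the non-randomised Hb comparison (hypothesis 2) can be biased by when women enter, in a direction the protocol does not fix.

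*Protocol*

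**What the plan says.** - **Entry (Protocol 6, criterion 1):** "Presenting for care after quickening and before onset of labor (i.e. in the second or third trimester of pregnancy". There is no upper gestational limit short of labour.
- **Testing (7.6.2.3 and 7.3.5):** "RDTs will be performed on maternal blood obtained by venipuncture at the time of each routine antenatal visit, and at the time of delivery". On spacing: "Routine visits will be scheduled at least 4 weeks apart; participants will not receive more than one dose of SP within any 4-week period". Section 5 describes the usual pattern as one test in the second and one in the third trimester. The 11.2 table has one RDT row for each of those trimesters and one for delivery.
- **Exposure class (11.2):** "RDT positive: a positive RDT result is obtained from one or more blood samples".
- **Hypothesis 2 (11.2):** "Mean Hb of mothers who were RDT positive & treated with ACT/quinine ≥ mean Hb of mothers who were RDT negative (and received SP".
- **Gestational age (7.6.5):** at enrolment "duration of gestation and expected delivery date will be estimated by reported last menstrual period (LMP", and by fundal height.
- **Adjustment (11.1):** factors "including iron and folate supplementation, bed net use and administration of antihelminthic drugs will be treated as confounders in the analysis". In the 11.2 table the confounder column marks site, age, gravidity, SP, iron/folate and bed net use. The last three are binary, for example "Iron & folate supplementation | Binary (yes/no". Gestational age appears nowhere in that table.

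**The concern.** Hypothesis 2 compares groups formed by test result, not by randomisation, so its validity rests on the adjustment set. Entry time acts on both sides of the comparison. It limits how many RDTs a woman can have, and so her chance of at least one positive. It also sets how many weeks of supplementation, net use, anaemia management and SP come before delivery Hb.

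The listed covariates do not cover this. Iron/folate and nets are offered to every participant (7.3.4), and RDT-positive women are also scheduled for SP after curative treatment (7.3.3, 7.4.3). Yes/no indicators of these will probably vary little, and they carry neither weeks nor number of doses. A difference in Hb between the RDT groups could then partly reflect when women enrolled.

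**Working it through.** **1. The plan's own figure.** Section 11.3 states a detectable Hb difference of 0.34 g/dL with 1,665 enrolled and 15% loss, so 1,665 × 0.85 ≈ 1,415 evaluable. The usual formula is (z_alpha + z_power) × SD × √(1/(np) + 1/(n(1−p))). The protocol gives neither the Hb SD nor the RDT-positive share p, so 0.34 cannot be reproduced. At two-sided 5% and 80% power it implies p of about 7.5%, 12% or 19% for assumed SDs of 1.2, 1.5 or 1.8 g/dL. That is plausible, and I use 0.34 only as a yardstick.

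**2. Mechanism in two groups.** Assume half the women enter early and half late, with no effect of malaria or treatment on Hb. Then:

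bias = [P(early | ever positive) − P(early | never positive)] × (Hb early − Hb late)

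*Equal positivity at every test.* Assume 10% per test, 3 tests for early and 2 for late entrants, and delivery Hb 0.5 g/dL higher in early entrants.
- Ever positive: early 1 − 0.9³ = 0.271; late 1 − 0.9² = 0.190.
- Share early among positives: 0.271/(0.271 + 0.190) = 0.588.
- Share early among negatives: 0.729/(0.729 + 0.810) = 0.474.
- Bias: (0.588 − 0.474) × 0.5 = +0.057 g/dL, favouring RDT positive.

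*Positivity falls after the first treated visit.* Assume 20% at the first test and 5% afterwards, with the same test counts and Hb gap. Early entrants: 1 − 0.80 × 0.95² = 0.278.

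| Late entrants' first-test positivity | Late ever positive | Bias (g/dL) |
|---|---|---|
| 20% | 0.240 | +0.025 |
| 24% | 0.278 | 0 |
| 30% | 0.335 | −0.034 |
| 35% | 0.383 | −0.059 |

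The break-even is 1 − 0.80 × 0.95 = 0.24. A modest excess of infection in women not yet given SP is enough to reverse the sign.

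**3. Size by simulation, no true effect.** All inputs are assumptions: entry uniform over 16–36 weeks, 12% preterm, 5–20% positive per test, and delivery Hb rising 0.02–0.04 g/dL per week of care.

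| Schedule | Spurious Hb difference (g/dL) |
|---|---|
| One test per trimester, no delivery test | +0.03 to +0.07 |
| Same, with delivery test | +0.02 to +0.05 |
| One per trimester, positivity falling from 20% to 5% after the first test | +0.01 to +0.02 |
| Every 4 weeks, upper end | about +0.15 |

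Against 0.34: 0.01/0.34 = 3%, 0.07/0.34 = 21%, 0.15/0.34 = 44%.

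**4. Effect of adjusting Hb.** Adding entry gestational age and its square took the difference from about +0.05 to +0.01 or less, and from about −0.02 to near 0, on the one-per-trimester schedule. With four-weekly tests it went from about +0.14 to +0.03. The correction works in either direction.

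**5. Birth weight behaves differently.** Under the any-positive class, a longer pregnancy also brings more tests. Adjusting for entry age alone enlarged the spurious difference: +29 g to +61 g in one scenario and +47 g to +65 g in another. With the enrolment RDT as exposure (positivity falling from 14% at 16–20 weeks to 7% at 32–36 weeks), it went from −14 g to −1 g.

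**The case against.** **The list in 11.1 is open, and covariates are often left to an analysis plan.** This is partly right. The wording in 11.1 is illustrative, antihelminthics are named there but not in the 11.2 table, and regression modelling is planned, so nothing excludes gestational age. But 11.2 goes further than a placeholder: it sets out a complete data set per pregnancy and assigns confounder roles. A covariate tied to both exposure class and outcome, and already collected, should be named there.

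**A reader might infer that the bias is anti-conservative, always favouring RDT-positive women.** The documents do not support that. It needs similar per-test positivity in early and late entrants, and longer care raising Hb; the protocol states neither. Section 7.3.3 says SP treats existing infection and protects against new infection, which points to higher positivity at first, untreated tests. Section 3.1.1 links infection to anaemia, so the net difference between groups may run the other way. Entry time is only one component.

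**A reader might also take 0.15 g/dL (44% of 0.34) as the expected size.** That needs four-weekly testing. The spacing rule in 7.3.5 permits it, but section 5 and the 11.2 table describe about one test per trimester.

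**Two limits stand.** Primary outcome 3 concerns placental malaria rather than RDT class, and these calculations do not model it. That the yes/no covariates vary little is also an inference: care is offered, actual use is recorded, and 7.6.1 allows extra iron for anaemia.

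**Conclusion.** The point holds as an omitted, measured confounder in the Hb comparison of hypothesis 2. It is a should-fix item and does not undermine the study. Its direction cannot be fixed from the protocol: it favours RDT-positive women if early and late entrants have similar positivity and longer care raises Hb, and it reverses if late entrants are clearly more often positive at their first test. Its size rests wholly on assumed inputs: about 0.01 to 0.07 g/dL (3–21% of 0.34) on the schedule the protocol describes as typical, and up to about 0.15 g/dL if visits are four-weekly. An unknown sign is a reason to adjust rather than to leave the covariate out.

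**What to change.** 1. Add gestational age at enrolment (weeks, continuous, from 7.6.5) to the confounder column of the 11.2 table, and include it with a non-linear term such as a quadratic in the maternal Hb regression.
2. For birth weight, do not simply add it to the any-positive comparison. Use it in one added analysis with the enrolment RDT result as exposure, and say that the pregnancy-length bias under the any-positive class is a separate problem that entry age does not remove.

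**Cost.** No new data are needed. The Hb part is a change of analysis wording; the birth-weight part adds one analysis. Dating by LMP and fundal height is imprecise, so the adjustment will be incomplete.
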